**2.2.2 Data Collection**

Routine clinical care for seriously ill patients with respiratory insufficiency will be followed as outlined by the primary physician. The study will log the results of monitoring labs consisting of complete blood count (CBC), electrolytes, glucose, BUN, serum creatinine, ionized calcium, magnesium, phosphorus, INR, albumin, liver function tests including of total bilirubin, aspartate alanine transaminase (ALT), and aspartate glutamine transaminase (AST), and complement studies (C3, C4, CH50). These laboratory tests will be logged from the closest available value (+/- 48 hours) on Days 0, 7, 14, 28 or at hospital discharge if < 28 days. In addition to the time points specified above, INR and Ionized calcium will be performed daily during the days when subjects undergoing PEX.

An extra 16 ml of blood needed for T-cell and B-cell studies for research purposes will be drawn at times corresponding to routine blood draws for clinical lab tests. These assays will be carried out in the laboratories of [name].

During hospitalization, subjects will be visited by study personnel within 24 hours after enrollment, and on Days, 7, 14, 28 (or on the day of discharge). A variance of two days will be allowed in the usual follow-up schedule. However, the 24 hour visit and discharge visit should occur on the specified day. In addition, a daily progress note will be made by the treating physician, and placed in the inpatient chart and research subject binder as a source document.

At these visits (Days 0, 7, 14, 28 or at hospital discharge), the following information will be collected and entered into to the study case report forms (CRFs). All clinical and laboratory data are part of routine clinical care and will be collected from medical records.

1. Demographics, physician names and contact information, general medical and surgical histories, co-morbidities, concurrent medications, and allergies.
2. Recording of vital signs and medication regimen.
3. Review of medication changes
4. Brief assessment of symptoms and documentation of any adverse effects.
5. Recording of laboratory and clinical testing results.

A telephone contact will occur on Day 60 for post treatment survival surveillance. If the subject remains inpatient, the assessment may be completed in the hospital setting. Subjects will be contacted by the study personnel to assess for symptoms potentially related to adverse effects of medications, review of medication changes, and interval medical or surgical histories including emergency or physician office visits. A variance of 3 days will be allowed for the telephone contact to facilitate scheduling or to account for weekends or holidays.

The schedule for patient assessment is outlined as follows (Appendix 2).

Day 0 (Enrollment):

- Informed Consent
- History and physical exam to include vital signs and blood pressure.
- Laboratory evaluations including complete blood count (CBC), electrolytes, glucose, BUN, serum creatinine, calcium, magnesium, phosphorus, albumin, liver function tests, and INR.
- Serology for hepatitis B (HbsAg).
- Assessment of PaO2.
- Complement studies of C3, C4, CH50.
- Assessment of peripheral blood T-cell and B-cell assays .

Day 7:

- Brief history and physical exam to include vital signs and blood pressure.
- Laboratory evaluations including complete blood count (CBC), electrolytes, glucose, BUN, serum creatinine, calcium, magnesium, phosphorus, albumin, liver function tests, and INR.
- Assessment of PaO2.
- Complement studies of C3, C4, CH50.
- Assessment of peripheral blood T-cell and B-cell assays.

Day 14:

- Brief history and physical exam to include vital signs and blood pressure.
- Laboratory evaluations including complete blood count (CBC), electrolytes, glucose, BUN, serum creatinine, calcium, magnesium, phosphorus, albumin, liver function tests, and INR.
- Assessment of PaO2.
- Complement studies of C3, C4, CH50. See above
- Assessment of peripheral blood T-cell and B-cell assays see above

Day 28 (or at hospital discharge if < 28 days):

- Brief history and physical exam to include vital signs and blood pressure.
- Laboratory evaluations including complete blood count (CBC), electrolytes, glucose, BUN, serum creatinine, calcium, magnesium, phosphorus, albumin, liver function tests, and INR.
- Assessment of PaO2.
- Complement studies of C3, C4, CH50.
- Assessment of peripheral blood T-cell and B-cell assays.

Day 60:

- Brief assessment of symptoms and documentation of adverse events, and a review of medical or surgical histories.

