**2.2 DETAILED DESCRIPTION OF RESEARCH ACTIVITIES**

**2.2.1 Study Design and Procedures**

The proposed combined treatment of plasma exchange (PEX), rituximab, and corticosteroids is routinely provided for a specific subset of patients with a unique form of autoimmune interstitial lung disease, called anti-synthetase syndrome or anti Jo-1 antibody syndrome at UPMC PUH. In this proposal, we plan to extend this treatment to the more general IPF exacerbation patient population which currently is most commonly treated with high dose corticosteroids or pulse solumedrol alone. All clinical and laboratory testing will be considered part of routine medical care for patients with no therapeutic options and a very high recognized mortality rate. In addition to routine medical care, specific T-cell and B-cell assays will be conducted in the laboratory of a Co-PI ([name]).

After hospital admission for acute IPF exacerbation (and after informed consent is obtained), subjects will receive the standard steroid treatment followed by initiation of the PEX and rituximab regimens. These latter two agents will require insertion of a dialysis/apheresis catheter into a central vein.

Standard Steroid Treatment: One gm of methylprednisolone i.v., on day 0, followed by 40 mg/day i.v. on days 1-4, and days 6-12 (or the p.o. prednisone equivalent). Methylprednisolone 100 mg i.v. will be administered on days 5 and 13. Steroid doses will then be 20 mg methylprednisolone i.v. (or p.o. prednisone equivalent) from days 14-28, and then reduced thereafter at the discretion of the principle investigator at each site. There are no published data that show efficacy of this agent at these doses. Nonetheless, steroid treatments (with highly varied doses and durations) are currently the standard of care for IPF patients with acute exacerbations.4 The high initial dose is intended to optimize early lympholysis. Administration of methylprednisolone 100 mg i.v. on days 5 and 13 will standardize steroid treatments among the two trial arms, as these agents are recommended prior to rituximab infusions.78 Steroid doses < 20 mg methylprednisolone i.v. (or p.o. prednisone equivalent) from days 14-28 are important to establish as this dose is an appropriate cutoff for consideration of lung transplantation.

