Plasma exchange (PEX) will consist of 1.5x estimated plasma volume exchanges for 3 successive days (0, 1,2) and then, after a one day interval to enable equilibration of autoantibodies sequestered in tissues, two more daily treatments on days 4 and 5. It is anticipated that fluid replacement with 5% albumin:normal saline (3:1 ratio), with a net fluid balance of 95-100%, will be possible in nearly all patients for the first two treatments. In the event a subject’s INR is >1.5 at the initiation of a PEX treatment, as may occur on the third or later treatment, the albumin:saline replacement will be partially supplanted with fresh frozen plasma (FFP) (anticipated to be <10 U/treatment) to maintain INR <1.6. The dialysis catheter will be removed after completion of the 5th and final PEX.

Rituximab: One gm i.v. will be administered on day 5 (after completion of the last PEX) and day 13. This regimen is adopted from the protocol of a recent large myositis trial at UPMC and other sites (NIHNO1 AR42273) and was well tolerated. Subjects will be treated with acetaminophen, antihistamines and methylprednisolone 100 mg i.v. prior to administration of rituximab to obviate reactions.75

The study design and flowchart is outlined in the table below (Appendix 1).

| Combined Treatment | **Days on Interventions** | | | | | | | | | |
| --- | --- | --- | --- | --- | --- | --- | --- | --- | --- | --- |
| **0** | **1** | **2** | **3** | **4** | **5** | **6-12** | **13** | **14-28** | **> 28** |
| Steroids | 1 gm /day, IV | 40 mg/day, IV  or oral Prednisone equivalent | | | | 100 mg  /day, IV | 40 mg/day, IV  or oral Prednisone equivalent | 100 mg  /day, IV | 20 mg/day, IV  or oral Prednisone equivalent | Tapering thereafter at the discretion of the treating physician |
| Plasma Exchange | 1.5x estimated plasma volume exchange/day | | | NA | 1.5x estimated plasma volume exchange/day | | NA | | | |
| Rituximab | NA | | | | | 1gm  /day, IV | NA | 1 gm  /day, IV | NA | |

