**3.2 INCLUSION CRITERIA**

The inclusion criteria have been selected to isolate a patient population with advanced idiopathic pulmonary fibrosis with a disease exacerbation. The exclusion criteria are selected to not enroll patients with an alternative cause for a respiratory decompensation (ie infection, pulmonary embolism) and to exclude patients with increased risk for the associated intervention (corticosteroids, plasmapheresis and ritiximab). Patients with a coagulopathy are excluded to minimize the risk of catheter insertion associated with the intervention.

1) A diagnosis of idiopathic pulmonary fibrosis that fulfills American Thoracic Society Consensus Criteria.1*

2) Unexplained worsening or development of dyspnea or hypoxemia within 30 days leading to the current hospitalization.

3) Radiographic imaging showing ground-glass abnormality and/or consolidation superimposed on a background of reticular or honeycomb pattern consistent with UIP.

4) Intent on the part of the treating physician to use high dose steroid therapy as a therapeutic effort to treat a diagnosis of acute IPF exacerbation.

In addition to strict adherence to current consensus criteria,1 IPF patients have serologic determinations of antinuclear antibody (ANA), rheumatoid factor (RF), anti-glomerular basement membrane antibody (AGBM), and anti-nuclear cytoplasmic antibodies (p-ANCA and c-ANCA) as standard of care diagnostic tests. Results of these serologic tests will be retrospectively used to substantiate the absence of confounding autoimmune syndromes in trial subjects, with implications for final data analyses and reporting.

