**3.3 EXCLUSION CRITERIA**

1. Diagnosis of documented infection based upon clinical evaluation and microbial testing.
2. Diagnosis of thromboembolic disease by clinical assessment.
3. Diagnosis of an additional etiology for ALI/ARDS based upon clinical assessment to include sepsis, aspiration, trauma, inhalational injury, acute pancreatitis, drug toxicity, blood product transfusion reaction, or stem cell transplantation.
4. Diagnosis of congestive heart failure that accounts for the hypoxemia.
5. Presence of active hepatitis B infection.
6. Coagulopathy defined as an INR > 1.8, PTT > 2 x control, and platelet count < 50K.
7. Hyperosmolar state or diabetic ketoacidosis to suggest uncontrolled diabetes mellitus or uncontrolled hypertension (systolic BP > 160 mm Hg and diastolic BP > 100 mm Hg) which would contraindicated the use of corticosteroids.
8. Hemodynamic instability defined as a vasopressor requirement which would contraindicate the use of plasmapheresis.
9. History of reaction to blood products, murine-derived products, or prior exposures to human-murine chimeric antibodies,
10. History of malignancy.
11. Inability or unwillingness to accept a blood transfusion.
12. Inability or unwillingness to complete post- treatment surveillance for 60 days.
13. Diagnosis of major comorbidities expected to interfere with subjects study participation for 60 days.

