Hematologic: Anemia (3-8%)

Local: Pain at the injection site (<5%)

Neuromuscular & skeletal: Back pain (10%), myalgia (10%), arthralgia (6% to 10%), paresthesia (2%), arthritis (<5%), hyperkinesia (<5%), hypertonia (<5%), neuropathy (<5%)

Ocular: Conjunctivitis (<5%), lacrimation disorder (<5%)

Respiratory: Throat irritation (2% to 9%), bronchospasm (8%), dyspnea (7%), upper respiratory tract infection (RA: 7%), sinusitis (6%)

Miscellaneous: LDH increased (7%)

Rare events associated with rituximab include severe mucocutaneous reactions, progressive multifocal leukoencephalopathy due to LC virus reactivation, hepatitis B reactivations, and other infections.78

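### Hepatitis B reactivation is a named rituximab risk, but HBsAg-only screening does not identify HBsAg-negative past or occult infection before rituximab is given

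*Protocol*

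**What the plan says.** Protocol section 3.2 gives the purpose of the exclusion criteria. Besides removing other causes of respiratory decline, they are meant "to exclude patients with increased risk for the associated intervention (corticosteroids, plasmapheresis and ritiximab". Section 5.1.2 lists, among the rare events with rituximab, "hepatitis B reactivations, and other infections".

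Two items act on hepatitis B. Exclusion 5 in section 3.3 reads "Presence of active hepatitis B infection". The Day 0 schedule in section 2.2.2 has "Serology for hepatitis B (HbsAg". No other hepatitis B test appears: the protocol mentions neither core antibody nor HBV DNA, antiviral prophylaxis or hepatitis B monitoring. The rituximab paragraph of section 5.5.2 deals only with premedication against infusion reactions.

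Rituximab dosing is in section 2.2.1: "One gm i.v. will be administered on day 5 (after completion of the last PEX) and day 13". Liver function tests are scheduled for Days 0, 7, 14 and 28, or at discharge if earlier (section 2.2.2). Day 60 has no laboratory work. It is a contact, usually by telephone, for "Brief assessment of symptoms and documentation of adverse events, and a review of medical or surgical histories".

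**The concern.** Reactivation, in the plain meaning of the word, is the return of an infection that was not active beforehand. The protocol names that event as a rituximab risk, then screens for and excludes only infection that is already active. A patient who is HBsAg-negative but has past or occult infection meets every hepatitis B requirement, and nothing in the plan prompts a decision on eligibility, prophylaxis or monitoring for that patient.

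What is at stake is the safety of such a patient and the ability to explain a late liver event if one occurs. With the core antibody result in hand beforehand, prophylaxis or targeted monitoring becomes possible.

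**Working it through.** The protocol states no figure that bears on this point, so there is none to reproduce. The check sets the sections side by side and then works out the timing.

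**Does the screen reach the named risk?**

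- Risk named: hepatitis B reactivation with rituximab (section 5.1.2).
- Purpose stated: keep out patients at increased risk from rituximab, among other treatments (section 3.2).
- Exclusion: active infection only (section 3.3, item 5).
- Test: HBsAg only (section 2.2.2, Day 0).

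HBsAg measures surface antigen that is present now. A carrier without active disease tests positive and is found, so the screen does reach some patients in whom reactivation could occur. A patient with past or occult infection and no detectable surface antigen tests negative and is not found. The screen therefore covers part of the named risk.

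**When does scheduled liver testing stop, relative to rituximab?**

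Inputs: second rituximab dose on Day 13 (section 2.2.1); last liver test on Day 28, or at discharge if earlier, with laboratory values taken within 48 hours either way (section 2.2.2); final contact on Day 60 with a 3-day variance (section 2.2.2).

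- Second dose to last liver test, subject still in hospital: 28 − 13 = 15 days; with the 48-hour window, 26 − 13 = 13 to 30 − 13 = 17 days.
- Second dose to final contact: 60 − 13 = 47 days; with the variance, 57 − 13 = 44 to 63 − 13 = 50 days.
- Last liver test to final contact, nominal: 60 − 28 = 32 days.
- The same gap at its shortest: 57 − 30 = 27 days.
- For discharge on a day d before Day 28, the nominal gap is 60 − d, which exceeds 32 days.

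**How much room is there before rituximab?**

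Exchanges are on Days 0, 1, 2, 4 and 5, and the first rituximab dose follows the fifth. A sample taken on Day 0 leaves five days for a result. The order of sampling and exchange matters. Exchange is used here to remove antibody (section 1.4), and fresh frozen plasma, which can carry donor antibody, may replace part of the fluid at later exchanges (section 2.2.1). An antibody test taken after exchange has begun could mislead in either direction.

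**The case against.** The strongest reply is that the plan contains no contradiction: HBsAg is a reasonable test for exclusion 5, and section 3.2 states a general purpose, not a promise to screen for every susceptibility to every rare event. That stands. A reader might infer that test and exclusion conflict, or that HBsAg screening is useless here. Neither is so. The exclusion and the test agree with each other; the shortfall is between both of them and the risk named in section 5.1.2.

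A second reply is that the documents do not say in which patients reactivation occurs, so the point leans on outside knowledge. This stands in part. The protocol gives no account of the mechanism, and some patients at risk are HBsAg-positive and would be caught. But that HBsAg does not detect HBsAg-negative infection follows from what the assay measures, and needs no remembered source.

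A third reply is that other safeguards exist. Day 0 includes a history, examination and liver tests. Visits include "Brief assessment of symptoms and documentation of any adverse effects". Section 5.4.2 has adverse events followed beyond the observation period if need be, and section 5.4.4 has the principal investigator review safety data as they arise. A past infection the patient knows of might come to light this way. These safeguards narrow the gap without closing it. No criterion acts on a history of hepatitis B, an unknown past infection stays unknown, and after Day 28 or discharge a silent rise in liver tests would surface only through symptoms or outside care.

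A reader might also infer that the steroid course ("One gm of methylprednisolone i.v., on day 0, followed by 40 mg/day i.v. on days 1-4, and days 6-12") adds to the harm chargeable to the trial. The documents do not support that. Section 2.2.1 describes steroids as current standard of care, and inclusion criterion 4 requires that the treating physician already intends high-dose steroids.

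**Conclusion.** The point holds as a gap in safety screening that should be closed because doing so is cheap. As written, the plan would give rituximab on Days 5 and 13 to an HBsAg-negative patient with past or occult hepatitis B without that patient being identified. It then schedules no liver test from Day 28 or discharge up to the Day 60 contact, nominally 32 days and at least 27.

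The conclusion rests on the risk the protocol itself names, on the plain meaning of reactivation, and on what HBsAg measures. It does not extend to a rate of harm: the documents give neither a prevalence of past infection nor a reactivation rate, and section 5.1.2 classes the event as rare. Nor does it touch the primary cardiopulmonary variables in section 2.3.1. A late liver event would still count as treatment-emergent under section 2.4.2 if it were reported.

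**What to change.** Add total hepatitis B core antibody to the Day 0 HBsAg sample. State that the sample is drawn before the first plasma exchange, and require the result before the first rituximab dose on Day 5. If core antibody is positive, send HBV DNA and hold rituximab until the DNA result is known. Then:

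- DNA positive: treat as active infection under exclusion 5 and give no rituximab.
- DNA negative: rituximab may proceed, either with antiviral prophylaxis or with scheduled liver tests and HBV DNA that continue after Day 28. The protocol should choose one of these in advance and, for monitoring, fix its frequency and duration.
- Keep any subject who has started exchange in the safety analysis.

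The cost is one extra assay per subject, 10 in all, on serology already planned for Day 0, and an occasional DNA test, including after a false-positive core antibody. Enrolment and the first exchange need not wait. The real downside is that a DNA-positive result arriving as late as Day 5 leaves a subject who has had steroids and up to five exchanges but gets no rituximab. One such subject would mean 10 − 1 = 9 of 10 could receive the full regimen. This does not arise if the results are available before the first exchange.

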**2.3 STUDY ENDPOINTS**

**2.3.1. The Primary End-Points**

The primary outcome measures for this study are the feasibility and safety of the regimen in patients with IPF exacerbations. Safety will be assessed by monitoring three variables of cardiopulmonary function:

- Respiratory deterioration defined as PaO2 on days 0, 3, 5, 7, 14, 28 (if still hospitalized) while breathing 100% FiO2 for >20 minutes by either endotracheal tube (ETT) or nonrebreathing face mask if not intubated (face masks and O2 delivery systems for nonintubated patients will be standardized).
- Hemodynamic deterioration defined as need for initiation of vasopressor agents, inotropes, or intravenous diuretics.

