We hypothesize that acute IPF is a manifestation of autoantibody-mediated lung injury, and that mechanistically-focused treatments will have better efficacy than nonspecific, current standard medical therapy. We further anticipate that our rituximab + PEX treatment will result in improved short-term mortality of IPF patients with acute exacerbations, enabling many more of them to survive long enough for definitive lung transplantation. As such, the experimental treatment proposed here will be a beneficial “bridge” to “buy time” for these otherwise doomed patients to benefit from curative lung transplantation.

- 1. **SPECIFIC AIMS**

1. To assess the feasibility and safety of combined PEX, rituximab, and conventional corticosteroid administrations for the treatment of hospitalized patients with acute IPF exacerbations by monitoring indices of respiratory (PaO2) and cardiovascular function during the treatment interval.

2. To assess the efficacy of combined PEX, rituximab, and conventional corticosteroid administrations for the treatment of hospitalized patients with acute IPF exacerbations on patient survival in comparison to historical controls. Patient survival for this investigation will be defined using the composite outcome of 60d survival and/or survival to lung transplantation.

**As such, more IPF patients with acute exacerbations will live long enough to have the clinical evaluations necessary for lung transplantation and until suitable donor organs can be procured.**

We hypothesize the combined treatment will ameliorate autoantibody-mediated lung injury and have a demonstrably beneficial effect on patient outcome.

- 1. **BACKGROUND**

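### The assessment schedule leaves out the day 3 and day 5 PaO2 that the primary respiratory safety endpoint requires

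*Protocol*

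**What the plan says.** Section 2.3.1 makes feasibility and safety the primary outcomes. Its respiratory component reads "Respiratory deterioration defined as PaO2 on days 0, 3, 5, 7, 14, 28 (if still hospitalized"), taken "while breathing 100% FiO2 for >20 minutes by either endotracheal tube (ETT) or nonrebreathing face mask if not intubated". Masks and oxygen delivery systems are to be standardised for patients who are not intubated. Specific Aim 1 says safety will be assessed "by monitoring indices of respiratory (PaO2) and cardiovascular function during the treatment interval".

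Section 2.2.2 governs collection. For the CRF it says "At these visits (Days 0, 7, 14, 28 or at hospital discharge), the following information will be collected". The day-by-day schedule that follows (labelled Appendix 2) carries the line "Assessment of PaO2" under Days 0, 7, 14 and 28. It has no Day 3 or Day 5 entry. A two-day variance applies to follow-up visits, but not to the 24-hour or discharge visit.

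On laboratory values, section 2.2.2 says "These laboratory tests will be logged from the closest available value (+/- 48 hours) on Days 0, 7, 14, 28 or at hospital discharge". The list includes complement (C3, C4, CH50) and does not include PaO2. INR and ionized calcium are to be measured daily on exchange days.

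Section 2.3.1 also states "Safety will be assessed by monitoring three variables of cardiopulmonary function". In the text available, two bullets follow: respiratory and hemodynamic deterioration.

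**The concern.** The endpoint and the schedule disagree on when the primary safety measurement is taken. The two days that drop out are the only endpoint days between the start of treatment and day 7. Day 3 follows the first block of exchanges. Day 5 carries the last exchange and the first rituximab infusion.

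Routine care may not fill the gap. Section 2.2.2 relies on medical records, but this endpoint is a standardised measurement on 100% oxygen. A blood gas taken on another oxygen fraction is not the endpoint.

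The population makes early values important. Section 1.1 says most such patients die within days to a few weeks, and section 1.3 gives hospital mortality of about 50%. A patient who dies before the Day 7 assessment could contribute only a Day 0 value, so the worst early courses would be the least observed. The mixed model for gas exchange in section 2.4.2, with random slope and intercept, would also have at most four scheduled values per patient instead of six.

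A separate question is whether the logged Day 0 laboratory values are a true baseline, because steroid and exchange both begin on day 0.

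**Working it through.** The protocol gives no figure to reproduce here. The check compares sets of days.

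**Inputs.** Endpoint PaO2 days come from 2.3.1. Scheduled PaO2 days and CRF visits come from 2.2.2. Exchange days (0, 1, 2, 4, 5) come from 2.2.1. The sample size of 10 comes from 2.4.1.

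| Day | Exchange | PaO2 in 2.3.1 | PaO2 in 2.2.2 schedule |
| --- | --- | --- | --- |
| 0 | yes | yes | yes |
| 1 | yes | no | no |
| 2 | yes | no | no |
| 3 | no | yes | **no** |
| 4 | yes | no | no |
| 5 | yes | yes | **no** |
| 7 | no | yes | yes |
| 14 | no | yes | yes |
| 28 | no | yes | yes |

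**Missing time points.** {0, 3, 5, 7, 14, 28} minus {0, 7, 14, 28} = {3, 5}, so 2 of 6 have no scheduled collection.

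**Values.** 10 × 6 = 60 at most under 2.3.1, and 10 × 4 = 40 at most under the schedule. The difference is up to 20. These are ceilings, because deaths and discharges reduce both counts.

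**Coverage of exchange days.** The schedule puts a PaO2 on 1 of 5 exchange days (day 0). The endpoint puts one on 2 of 5 (days 0 and 5).

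**Can the visit variance close the gap?** The Day 7 visit may fall on days 7 − 2 = 5 to 7 + 2 = 9. A visit on day 5 is allowed, but its value would replace the Day 7 value, not add to it. Day 3 is outside the window.

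**Day 0 laboratory window.** ±48 hours around day 0 runs from day −2 to day +2. Exchanges fall on days 0, 1 and 2, and the first steroid dose on day 0. An accepted Day 0 value can therefore follow steroid and up to three exchanges. The rule picks the closest value without regard to treatment: if the only values are from day −2 and day +1, it selects day +1, after treatment has begun, over the available pre-treatment value.

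**The case against.** The strongest reply is that section 2.3.1 is itself binding protocol text. It fixes the days, the oxygen fraction, the duration and the delivery system. On that view the gases will be taken, and because CRF data come from the chart, the day 3 and day 5 results could be entered at the Day 7 visit. This stands in part: a reader might infer that the values are lost, and the documents do not show that. They show that no visit, schedule line or CRF time point plans for them.

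A reader might also infer that the exchange days go unmeasured. They do not. PaO2 is scheduled on day 0, which is an exchange day. INR and ionized calcium are measured daily on exchange days, and a daily physician note is kept as a source document. Of the two omitted days, only day 5 is an exchange day; day 3 is the rest day. None of this supplies the missing PaO2.

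On the Day 0 laboratory values, several protections are in place. The closest-value rule makes the three-exchange case an extreme one, and the schedule places these tests at enrollment beside consent. INR and platelets must be known for the coagulopathy exclusion, and INR is then tracked daily during exchange. Albumin is part of the replacement fluid, so simple washout reasoning does not apply to it. What remains is chiefly complement, which is not listed as an endpoint. The window covers the listed laboratory tests and not PaO2, so it plays no part in the PaO2 gap.

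Finally, the count of three variables may reflect a bullet lost when the text was extracted.

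**Conclusion.** The contradiction on the primary safety endpoint is real. Sections 2.3.1 and 2.2.2 give different PaO2 days. Under the schedule, 2 of 6 endpoint time points (up to 20 of 60 values) have no planned collection. No PaO2 is scheduled between day 0 and the Day 7 visit, which can fall on day 5 at the earliest. The size assumes that all 10 patients are enrolled and remain in hospital, and that staff work from the visit schedule and not from the endpoint definition. If gases are taken under 2.3.1 and entered later, fewer values would be missing.

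The Day 0 laboratory window is a secondary weakness, confined mainly to complement. A reader might infer that it also undermines the adverse-event comparison. The documents do not support that directly: section 2.4.2 defines treatment-emergent events by enrollment and by severity over a baseline period, not by the logged Day 0 laboratory value.

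The mismatch between three variables and two is a minor wording point.

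**What to change.** 1. Reconcile sections 2.2.2 and 2.3.1. Add the day 3 and day 5 PaO2 on 100% oxygen, which 2.3.1 already requires, to the assessment schedule (Appendix 2) and to the CRF.
2. State that the logged Day 0 laboratory value is the last one before the first study treatment.
3. In 2.3.1, name the third safety variable or correct the count to two.

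The cost is a few lines of protocol text and CRF fields for two more time points. The first change adds no blood gas beyond those 2.3.1 already calls for. The second changes which existing value is logged, and needs a draw before treatment only where none has been done.
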